There is a continuing attempt to compare the efficacy and safety of the various COH protocols [2,3]. Their implementation, based on the administration of agonists of gonadotropin-releasing hormone (GnRH) (“long”), likely leads to comparable live birth rates (LBR) to those based on the GnRH antagonists (“short”). The latter reduces the probability of ovarian hyperstimulation syndrome (OHSS) in predicted normal or high responders [4,5,6]. The use of rFSH in COH in normal responders undergoing the “long” GnRH agonist protocols may also lead to lower fresh-cycle LBR compared to that of when hMG is used [5]. However, there are certain noteworthy limitations of the existing very low- to low-certainty evidence. Such include the lack of high-quality trials, the inclusion of unspecified populations of infertile couples in the vast majority of trials, and the insufficiency of data to allow separate estimations for poor and high responders or comparison of all possible combinations of GnRH agonists/antagonists with the gonadotrophin preparations and triggering agents [4,5]. The significant inconsistency between studied populations and interventions applies to most of the literature on assisted reproductive techniques (ART). Furthermore, it has been identified as one of the main research-related factors responsible for the plateauing of ART success rates [7,8]. Further potential reasons include flaws in the design, execution, and/or reporting of the current studies, as well as factors linked with issues related to clinical practice, such as the lack of the true efficacy of “add-on” treatments and the “industrialization” of IVF [7,8,9]. It therefore seems that the exploration and the proper use of markers that could provide clinicians with a more individualized picture of a patient’s probability of an adequate response to a specific COH protocol are, nowadays, crucial [10,11,12,13].

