### 1.2. The mTOR-Related Pathways in Ovarian GC

mTOR is a serine-threonine kinase that acts as the active catalytic subunit of two intracellular complexes, namely, the mTOR complex 1 and mTOR complex 2. A plethora of studies have demonstrated that mTOR may be activated by multiple signaling pathways within the ovarian GCs, including the PI3K/Akt and the cyclic adenosine monophosphate (cAMP)/cAMP-dependent protein kinase A (PKA)/mitogen-activated protein kinase (MAPK)/extracellular signal-regulated kinases (ERK) [14,15,16,17,18,19]. These exhibit dynamic interactions with one another and can be activated by various factors, including the FSH, the epidermal growth factor (EGF), the vascular epithelial growth factor (VEGF), and the insulin or insulin growth factor-1 (IGF-I) [14,16,19,20,21]. Ribosomal protein S6 kinase beta-1 (p70S6K-1) and eukaryotic translation initiation factor 4E (eIF4E) are the main downstream effectors of the mTOR pathway [15,22,23].

Accumulating evidence from in vitro studies or animal models has demonstrated that the stimulation of mTOR and its downstream effectors in ovarian GCs may orchestrate the processes of quiescence, activation, and survival of primordial follicles; induce proliferation and differentiation of GCs and meiotic maturation of oocytes [24,25,26]; and suppress the phenomena of autophagy and apoptosis [27,28,29,30]. The activation of mTOR via the described pathways seems to be an essential mediator for the bidirectional communication between GCs and oocytes. These interactions lead to a nurturing microenvironment for follicular growth, which in turn empowers the oocyte’s developmental potential [31,32,33,34]. A better oocyte developmental competence is associated with an increased ability of the oocyte to complete meiosis and, subsequently, undergo fertilization, implantation, embryogenesis, and term development [31,33]. In contrast, the overactivation of mTOR-related pathways in in vitro or animal studies has been associated with ovarian aging and the pathogenesis of premature ovarian insufficiency due to massive maturation of primordial follicles [35,36], polycystic ovary syndrome (PCOS) [37,38], endometriosis [39], and ovarian cancers [40,41,42]. In the same context, its inhibition may lead to an increase in ovarian reserve and lifespan [43,44] and the mitigation of OHSS symptom severity [45].

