## 2. Objectives

In this paper, we aim to express the hypothesis that the activity of both the mTOR (the mechanistic target of rapamycin) and Hippo pathways within the GCs isolated by the follicular fluid of women undergoing IVF may be affected by the type of protocol used for COH; these differences in activity may also influence the outcomes of the IVF cycle. As discussed above, these pathways orchestrate the processes of proliferation, differentiation, and apoptosis of GCs. Such processes are directly related to the development and maturation of the follicles, the quality of the oocytes, and potentially, the outcomes of the IVF cycle. Data to form this hypothesis currently derive from in vitro/animal studies; thus, this study design involving humans is original in the literature.

To initially test the potential validity of this hypothesis, we propose the measurement of the activity of the two pathways through the levels of the phosphorylated/unphosphorylated forms of specific proteins: i. mTOR, p70S6K-1 to reflect the downstream activation of mTOR-related pathways and ii. YAP-1, TAZ to reflect the activation of Hippo. The phosphorylated forms of mTOR and p70S6K-1 represent the increased activation of the mTOR-related signaling pathways, whereas the decreased phosphorylated and elevated unphosphorylated levels of YAP-1 and TAZ signify the Hippo inhibition, and therefore intensified the signals for GC proliferation. Levels of these forms will be compared between GCs isolated from the follicular fluids of women receiving GnRH agonists and those receiving GnRH antagonists for pituitary suppression. This first stage of the study will be conducted prospectively.

We further aim to compare these measurements between women achieving positive IVF outcomes and those who did not. In this way, we will attempt to examine whether the potential differences in the activity of the two pathways could be correlated with the final (primary and/or secondary) outcomes of the IVF cycle. This second stage will be conducted through a case-control design. The study is aimed to be divided into an initial pilot phase, during which the feasibility of the design will be assessed, and a final phase, during which a growing registry is to be created where additional subgroup analyses (addressing the inconsistency of the population) are to be conducted.

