## 3. Materials and Methods

### 3.1. Study Design

Comparison of the phosphorylated/unphosphorylated levels of the pathways’ components following the administration of GnRH antagonist/“short” protocols versus GnRH agonist/“long 21” protocols will be conducted through a prospective-cohort design. A comparison of levels between women achieving certain predefined outcomes within the IVF cycle and those not reaching these outcomes will be carried out through a case-control design. The pilot phase of the study, during which 100 women undergoing IVF are planned to be recruited, will be conducted in the Second Department of Obstetrics and Gynecology of “Aretaieion Hospital”, Athens, Greece, a tertiary academic center within a university IVF unit (Figure 1). Institutional review board approval will be received, and informed consent will be obtained from all participants. Following the potential success of the pilot phase, more public/private study centers are to be added towards the increased recruitment of the study subjects.

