### 3.2. Eligibility Criteria and Data Collection

All women aged 30–40 years old undergoing IVF due to female/male factor or unexplained infertility will be considered eligible for the study. Advanced age has been identified as a negative factor for IVF success rates. The limit is around 40 years of age. After this age, a steep decline in pregnancy and delivery rates are observed [61,62]. As noted above, and based on the currently available evidence, GnRH agonist and GnRH antagonist COH protocols lead to comparable live birth rates [4]. For all these reasons, we chose to include women in the age range of 30 to 40. Two protocols of i. GnRH agonists and ii. GnRH antagonists for pituitary suppression, following stimulation with r-hFSH, will be administered to participants.

For the GnRH agonist protocol, Triptorelin [Gonapeptyl, 3.75 mg (Ferring Pharmaceutical Hellas A.Ε.) or Arvekap, 3.75 mg (Ipsen, EPE)] will be administered subcutaneously daily during the midluteal phase of the menstrual cycle.

For the GnRH antagonist protocol, ovarian stimulation will begin on the second day of the cycle, and the antagonist, either Cetrorelix (Merck Serono Europe Limited, Middlesex, UK) or Orgalutran (Merck Sharp & Dohme Limited, Hoddesdon, UK), will be initiated as soon as the leading follicle reaches a diameter of 14 mm. Once pituitary downregulation and ovarian suppression is achieved, ovarian stimulation with exogenous gonadotropins will start, while GnRH agonist administration will continue concomitantly until the day of hCG administration. Recombinant FSH in the form of either follitropin alpha (Gonal-F; Merck Serono Europe Ltd, London, UK) or follitropin beta (Puregon; Merck Sharp & Dohme Ltd., Hertfordshire, UK) will be administered subcutaneously.

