### 3.5. Data Analysis

Categorical variables will be presented as frequencies and percentages, whereas numerical variables will be presented as mean (standard deviation) or median (interquartile range) based on the normality of the data. A normality check will be performed by using the Shapiro–Wilk test. Independent samples *t*-test or Mann–Whitney U test (as per normality or not of data) will be utilized for comparisons regarding numerical variables, whereas chi-square or Fisher’s exact (if applicable) tests will be used for categorical variables. Following the pilot phase (during which the following analyses would be underpowered), further analyses are being planned. Comparisons of the pathways’ activity will be made by patients’ age (<35 vs. >35 years of age), by category of infertility (male, female, or unexplained), and by the female infertility-related factor (e.g., PCOS and endometriosis). Concerning the IVF outcomes, multivariable logistic regression models are further being planned.

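### The pilot's marker-versus-outcome comparison is unadjusted for protocol and age, and lack of power does not justify leaving out two covariates

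*Protocol article*

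**What the plan says.** Section 3.1 sets the size: "The pilot phase of the study, during which 100 women undergoing IVF are planned to be recruited". It describes a prospective cohort for the protocol comparison and a case-control comparison of the same women by IVF outcome. It mentions neither randomisation nor any rule for who receives which protocol.

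Section 2 states two linked hypotheses: that pathway activity "may be affected by the type of protocol used for COH", and that "these differences in activity may also influence the outcomes of the IVF cycle".

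Section 3.4 makes live birth the primary outcome of the case-control part and lists OHSS among the secondary outcomes. Neither that section nor the legend to Figure 1 separates women by protocol when they are grouped by outcome.

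For numerical variables, section 3.5 names the t-test or the Mann-Whitney test. It then says: "Following the pilot phase (during which the following analyses would be underpowered), further analyses are being planned". What is postponed comprises comparisons of pathway activity by age, infertility category and female factor, and multivariable logistic models for the IVF outcomes. The covariates of those models are not named.

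The background statements that matter here are:
- Protocol and OHSS (section 1.1, on antagonist protocols): "The latter reduces the probability of ovarian hyperstimulation syndrome (OHSS) in predicted normal or high responders".
- Protocol and live birth (section 3.2): "GnRH agonist and GnRH antagonist COH protocols lead to comparable live birth rates".
- Age and outcome (section 3.2): "Advanced age has been identified as a negative factor for IVF success rates".
- Age and markers (section 1.2): "the overactivation of mTOR-related pathways in in vitro or animal studies has been associated with ovarian aging".

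**The concern.** A two-sample test of marker level by outcome answers the intended question only if nothing else drives both marker and outcome. The article itself supplies candidates. Protocol is hypothesised to move the markers and is said to alter OHSS risk. Age is said to lower IVF success, and the investigators think a relation between age and pathway activity plausible enough to plan a comparison on it. With no allocation rule, protocol could also follow prognosis.

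The reason given for postponing adjustment is power. That is a sound argument against subgroup analyses and models with many terms in 100 women. It does not obviously apply to two covariates, both of which are already recorded. At stake is a pilot that reports a marker-outcome association which is partly or wholly an effect of age or protocol.

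**Working it through.** The article gives no significance level, power, effect size, standard deviation (SD), event rate or protocol split, so it has no figure to reproduce. **Assumptions throughout:** two-sided 5% level, 50 women per protocol, marker differences in within-protocol SD, and no true marker effect unless stated.

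**1. Bias from protocol.** If protocol shifts the marker by *d* SD, the spurious difference between outcome groups is

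*d* × [P(protocol | outcome) − P(protocol | no outcome)].

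*Live birth, equal rates (30% and 30%).* Both probabilities are 0.5, so the bias is 0 whatever *d* is. Simulated false-positive rates (4,000 runs, t-test) were 5.2%, 4.9% and 4.8% at *d* = 0.5, 0.8 and 1.0.

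*Live birth, protocol chosen by prognosis.* Assume live birth of 40% in good-prognosis and 20% in poor-prognosis women (half each), *d* = 0.8, and 80% steered. The rates by protocol are then 0.8×0.40 + 0.2×0.20 = 36% and 24%. The bias is 0.8 × (0.36/0.60 − 0.64/1.40) = 0.8 × 0.143 = 0.11 SD. With 60% steered it is 0.04 SD.

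*OHSS (assumed rates).*

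| Rates | *d* | Spurious difference | False positives |
|---|---|---|---|
| 10% / 5% | 0.8 | 0.8 × (0.100/0.150 − 0.900/1.850) = 0.14 SD | 6.1% |
| 12% / 4% | 0.8 | 0.8 × (0.120/0.160 − 0.880/1.840) = 0.22 SD | 8.4% |
| 8% / 3% | 0.6 | 0.6 × (0.080/0.110 − 0.920/1.890) = 0.14 SD | not run |

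In the last row about 5.5 events are expected, and the standard error of the marker difference is √(1/5.5 + 1/94.5) = 0.44 SD. The bias is about a third of that.

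**2. Bias from age, live birth.** Assume age uniform on 30 to 40 and live birth falling from 38% to 12%, which gives about 23 live births per 100. Simulation with the Mann-Whitney test, n = 100, 4,000 runs:

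| Marker-age correlation | Spurious difference | Unadjusted false positives |
|---|---|---|
| 0.1 | 0.04 SD | about 5% |
| 0.2 | 0.09 SD | about 6% |
| 0.3 | 0.13 SD | about 8% |
| 0.5 | 0.21 SD | about 14% |

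With age in the model the false-positive rate is about 4% to 5% in every row.

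For scale, the difference detectable with 80% power is (1.960 + 0.842) × √(1/20 + 1/80) = 0.70 SD with 20 live births, and 2.802 × √(1/35 + 1/65) = 0.59 SD with 35.

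**3. Cost of adjusting.** With 20 to 35 live births, three parameters (marker, protocol, age) leave 20/3 = 6.7 to 35/3 = 11.7 events per parameter. Power was simulated with a linear model of marker on outcome, 30% live birth, a true difference of 0.6 SD, and age unrelated to either:

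| Protocol shift in marker | Unadjusted | Adjusted for protocol and age |
|---|---|---|
| 0 | 77% | 76% |
| 0.5 SD | 74% | 77% |
| 0.8 SD | 70% | 75% |

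Adjustment costs about one percentage point if protocol does not move the markers, and gains power if it does.

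**The case against.** The strongest reply concerns the primary outcome. A reader might infer that the comparison is confounded by protocol whenever the first hypothesis is true. The article does not support that. A protocol effect on the marker is necessary but not sufficient: protocol must also relate to outcome by a route other than the marker. The article states comparable live birth rates, and at equal rates the bias is zero. If protocol acts on outcome only through the pathways, as the two hypotheses together suggest, that is mediation and not confounding. This objection stands. It leaves open prognosis-driven choice of protocol, because similar rates in the cited evidence do not ensure similar crude rates in a non-randomised cohort.

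The age argument is also thinner than it looks. Section 1.2 concerns in vitro and animal work on ovarian ageing, not chronological age within a 30-to-40 window, and section 3.2 places the steep decline after about 40. The live birth gradient and the correlations used above are assumptions. This too stands, and it is why the result is given as a range that starts near no effect.

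Two further inferences should be resisted. One is that the pilot's marker-outcome result decides expansion to more centres: section 2 says the pilot assesses feasibility, section 3.1 ties expansion to an undefined success, and section 4 calls for many more studies before conclusions. The other is that the inflation will grow with the larger registry: multivariable models are planned for that stage.

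Finally, covariate lists are commonly left to a full protocol or analysis plan, so their absence is not the point. The point is the stated decision to postpone adjustment and the reason given. Nothing in the objections rescues that reason for a two-covariate set.

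**Conclusion.** The point holds in a limited form. The pilot's outcome comparison is described as pooled and unadjusted, and the power argument for postponing all multivariable modelling does not cover protocol and age.

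The possible distortion is modest. For live birth, age gives about 8% to 14% false positives instead of 5% if the marker-age correlation is 0.3 to 0.5, and about 6% at 0.2. Protocol contributes nothing to live birth unless its choice follows prognosis, in which case the assumed scenarios give 0.04 to 0.11 SD. For OHSS the assumed rates give 0.14 to 0.22 SD, with false-positive rates of 6% to 8% where simulated, on very few events. All rates, shifts, correlations and the even split are assumptions. The feasibility purpose of the pilot lowers the consequence, but the remedy is nearly free.

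**What to change.** In section 3.5, for the pilot:

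- Report the live-birth comparison from a logistic regression on marker level with protocol and age (continuous) as named covariates, alongside the unadjusted test. Use a Firth penalty if events are sparse.
- For sparse endpoints such as OHSS, use a rank test stratified by protocol (van Elteren) in place of the pooled test.
- State that the same two covariates enter the later multivariable models.
- Keep the subgroup comparisons and any larger covariate set for the final phase, where the power argument is sound.

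Section 3.2 already collects age, and protocol defines the study groups, so no new data are needed. The cost is a change of wording, slightly more analysis work and a small loss of precision.

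Stating how women come to receive each protocol would also let readers judge whether the choice follows prognosis.

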The upper goal of this research effort is to investigate whether measuring the activity of these intracellular pathways can somehow predict the ovarian response to COH protocols and/or final IVF outcomes by reflecting a more personalized state of the microenvironment of the ovarian GCs. The need for immediate study and further knowledge of these paths arises from the growing expectations of infertile couples to increase the chance of successful outcomes at the lowest possible financial cost while minimizing clinical procedures (reduction of the number of IVF attempts) and/or the probability of unwanted outcomes (e.g., miscarriage, ectopic pregnancy, and OHSS).

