Women outside the age span mentioned above or those undergoing natural or mild IVF protocols will be excluded from the study. The following patient data will be collected: age; BMI; type of infertility (i.e., male, female, or unexplained); relevant comorbidities associated with infertility (e.g., ovulatory disorders such as PCOS, tubal factors, or endometriosis); data from previous IVF cycles; levels of anti-Mullerian hormone (AMH); FSH; LH; prolactin; AFC; estradiol (E2) and serum progesterone in the early follicular phase; and data on the IVF cycle of the pathways’ measurements, such as the number and size of follicles at the time of triggering, and the number of aspirated follicles and oocytes retrieved. Successful or unwanted outcomes of the IVF cycle of the pathways’ measurements will also be recorded. Data will be collected within a secure online platform, further ensuring patient anonymity. Access to the platform will be granted strictly to members involved in the collection, analysis, or interpretation of data.

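### The post-pilot analyses of pathway levels make no stated use of AMH and AFC, which are already collected and bear on the paper's interest in individual ovarian response

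*Protocol article*

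**What the plan says.** **Rationale.** Section 1.1 lists several limits of the published comparisons of stimulation protocols. One is "the insufficiency of data to allow separate estimations for poor and high responders". The same section ties a protocol difference to responder class when it describes antagonist protocols: "The latter reduces the probability of ovarian hyperstimulation syndrome (OHSS) in predicted normal or high responders". It then argues for markers that give "a more individualized picture of a patient’s probability of an adequate response to a specific COH protocol".

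**Goal.** Section 2 asks whether measuring the pathways "can somehow predict the ovarian response to COH protocols and/or final IVF outcomes".

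**Population and data.** Section 3.2 states: "All women aged 30–40 years old undergoing IVF due to female/male factor or unexplained infertility will be considered eligible for the study". The only exclusions are age outside that range and natural or mild protocols. AMH and AFC are on the list of patient data to be collected, together with FSH and the yield of the cycle.

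**Analysis.** Section 3.5 compares numerical variables by t-test or Mann-Whitney test. For the period after the pilot it adds comparisons of pathway activity by "<35 vs. >35 years of age), by category of infertility (male, female, or unexplained), and by the female infertility-related factor", with PCOS and endometriosis as examples of the last. Multivariable logistic models are planned for the IVF outcomes, with no covariates named. Section 4 describes the later stratification again as age groups and aetiology of infertility.

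**The concern.** The paper names responder class as something earlier evidence could not separate and takes ovarian response as one of its targets. It then states its strata in two places without using the two collected variables that most directly describe expected response.

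Two things are at stake, both in the analysis of pathway levels by protocol:

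- **Effect modification.** If the agonist-antagonist difference in phosphorylation depends on ovarian reserve, an average over all women understates it where it exists and may hide it altogether.
- **Confounding.** Section 3.1 describes a prospective cohort and mentions no randomisation. The protocol groups may therefore differ in AMH and AFC, and the planned two-group tests would not separate that difference from an effect of the protocol.

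**Working it through.** The plan gives no figure to reproduce here. Its only sample size is the 100 women of the pilot, and the point does not depend on it. The check sets the sections side by side.

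1. *Is responder class part of the rationale?* Yes. It is one of several limits in section 1.1; the others include few high-quality trials, unspecified populations and untested drug combinations.
2. *Is ovarian response a target?* Yes, in section 2, together with IVF outcomes.
3. *Are women admitted regardless of ovarian reserve?* Yes. Section 3.2 has no AMH, AFC or responder criterion for entry or exclusion.
4. *Are the needed variables collected?* Yes, AMH and AFC are both listed in section 3.2.
5. *Are they used in a stated analysis of pathway levels?* No. Section 3.5 and section 4 name age, infertility category and female factor only. PCOS may overlap with high response, but it is not presented as a responder stratum, and no listed stratum identifies poor responders.
6. *Could the logistic models fill the gap?* Only in part. They might include AMH or AFC, but as written they concern IVF outcomes, not the comparison of pathway levels between protocols.

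**Illustration of dilution.** The documents give neither the mix of responders nor an effect size, so every input here is an assumption. Suppose a class makes up the same share of both protocol groups and is the only class with a difference. Then

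pooled difference = share × within-class difference.

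With an assumed within-class difference of 0.6 SD:

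| Assumed share | Pooled difference |
|---|---|
| 15% | 0.15 × 0.6 = 0.09 SD |
| 25% | 0.25 × 0.6 = 0.15 SD |
| 40% | 0.40 × 0.6 = 0.24 SD |

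If two classes of equal share *s* have opposite differences +*d* and −*d*, and there is no difference elsewhere, the pooled value is *s* × *d* − *s* × *d* = 0.

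**Confounding.** If the share of a class differs between protocol groups and the marker differs between classes, the unadjusted comparison carries an extra term: (difference in share) × (difference in marker between classes). The documents supply neither factor, so no size is given.

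**The case against.** A reader might infer that the paper contradicts itself: it faults others for not separating responders and then does the same. The documents do not support that. Section 1.1 goes on to set out the paper's own hypothesis about heterogeneity, in terms of demographic factors and types of infertility such as ovulatory or tubal disorders and endometriosis. The strata in section 3.5 follow that hypothesis closely. No stated aim promises separate estimates for poor and high responders.

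A reader might also infer that the finished registry must leave the responder question open. That does not follow either. AMH and AFC are recorded, the later phase is only outlined, and the strata are not declared a closed list. The responder analysis can still be specified before that phase begins.

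Three further objections have force. The dilution arithmetic would apply to any unlisted modifier, and nothing in the document shows that the pathway difference depends on responder class. The document does not itself say that AMH and AFC define predicted response. And a condensed article may leave the full list of subgroups and covariates to other documents.

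These points reduce the weight of the concern but do not remove it. The article chose to state its strata, did so twice, and both times left out a factor that its own rationale raises. The absence of any stated adjustment in the comparison of pathway levels by protocol does not depend on the infertility-type hypothesis at all.

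**Conclusion.** The point stands as a modest improvement. The plan collects AMH and AFC, admits women across the range of ovarian reserve, and is interested in individual response, but no stated analysis of pathway levels uses these variables as modifier or covariate. It is not an internal contradiction. The pilot, which has no subgroup analysis, is not invalidated.

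The size of any loss is unknown. The 0.09 to 0.24 SD range rests wholly on assumed shares and an assumed 0.6 SD effect, and should not be read as what this study would see. The conclusion also assumes that AMH and AFC are reasonable baseline indicators of expected response, and that protocol choice is not randomised, as the cohort description implies.

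**What to change.** In section 3.5:

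- Add baseline AMH and AFC, taken before stimulation and preferably kept continuous, as covariates in the post-pilot analyses of pathway levels by protocol.
- Add a protocol-by-AMH/AFC term to the same analyses, labelled exploratory. If classes are wanted for presentation, fix the cut-offs before the marker data are seen.
- In the pilot, report AMH and AFC by protocol group descriptively, without testing, so that any imbalance between the groups is visible.

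Section 4 should then mention the same variables alongside age and aetiology. The change needs wording only and no new measurement. The downside is one more exploratory modifier, repeated across four proteins on top of three existing stratifications, so its results should be read as hypothesis-generating.
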